#### 6. Handling missing data

No missing data will affect the primary and secondary outcomes. The number of subjects with non-missing values in each demographic variable will be reported in the tables comparing the two groups.

#### 7. Interim analysis

Not applicable

#### 8. Software & output

All statistical analyses will be carried out in R version 4.2.2.

## Summary of changes between final and original statistical analysis plan from protocol

### V1.3, dated 10.08.2022

#### Sample size:

The sample size calculation originally described in the protocol V1.3, dated 10.08.2022 was slightly revised as follows . The revised calculation assumed an intraclass correlation coefficient of 0.2 to account for family effects. This translates into 95% prediction intervals for family-specific participation probabilities of 9 - 22% in the control arm, and 20 - 41% in the intervention arm. With these adjustment, the required sample size increased to 44 families per arm (vs 41 in the protocol V1.3, dated 10.08.2022).

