## **5 STATISTICS AND METHODOLOGY**

### **5.1. Statistical analysis plan and sample size calculation**

The sample size has been calculated according to the primary outcome, for each of the study groups, monogenic *positive* and *negative* FH. The statistician team of Unisanté ([name] and [name]) has estimated the sample size.

The aim of the study is to show that the proportion of people who agree to do the screening is higher in the experimental group than in the control group. Consents and refusals being measured within the families, the observations are not independent. Thus, it would be inappropriate to compare the consent rates of the control and experimental groups using a chi-square test. To account for the effect of clusters, proportions will be compared using an odds ratio that will be estimated using a logistic regression model. The latter will include the group as a fixed effect (the parameter of interest) and the family as a random effect.

For the monogenic *positive* FH group, we calculated that it will be necessary to include 41 families per group to show a statistically significant difference between the two groups with a significance level of 5% and a power of 90%, assuming that the consent rates for the control and interventional groups will be in mean equal to 0.15 respectively 0.3 and will be at 95% in the intervals [0.1,0.2] (range 0.05) respectively [0.1,0.5] (range 0.2) and that the number of contactable relatives will be in mean equal to 4.

For the monogenic *negative* FH group, we calculated that it will be necessary to include 36 families per group to show a statistically significant difference between the two groups with a significance level of 5% and a power of 90%, assuming that the consent rates for the control and interventional groups will be in mean equal to 0.5 respectively 0.7 and will be at 95% in the intervals [0.30,0.70] (range 0.4) respectively [0.46,0.86] (range 0.4) and that the number of contactable relatives will be in mean equal to 4.

These sample sizes were calculated analytically based on the standard errors of the mean proportions and were verified using simulations.

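### The stated ICC of 0.2 does not give the family prediction intervals printed with it; they correspond to about 0.02 on the latent logit scale

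*Combined protocol and SAP*

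**What the plan says.** The sample-size paragraph in the final SAP's summary of changes holds the whole revised calculation. The numbered SAP sections contain no other justification. It gives three linked figures:

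- The clustering assumption: "The revised calculation assumed an intraclass correlation coefficient of 0.2 to account for family effects".
- Its stated consequence: "95% prediction intervals for family-specific participation probabilities of 9 - 22% in the control arm, and 20 - 41% in the intervention arm".
- The result: "the required sample size increased to 44 families per arm", up from 41.

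The paragraph does not name the scale of the ICC. It does not restate the error rate, power, participation rates or family size either. Because it presents itself as a slight revision, these are taken from protocol section 5.1: a "significance level of 5% and a power of 90" per cent, mean rates for the control and "interventional groups will be in mean equal to 0.15 respectively 0.3", and an average of four relatives per family who can be contacted. Neither document says whether the 5% is one-sided or two-sided.

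**The concern.** Families are randomised and relatives are analysed, so the intra-family correlation is the key planning assumption for the sample size. An ICC of 0.2 means that families differ widely in their willingness to be tested. The printed intervals describe families that differ rather little: control families nearly all between 9% and 22%. Both cannot describe the same family effect.

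What is at stake depends on which figure is wrong. If the calculation used 0.02, the plan tells readers that it allowed for ten times more clustering than it did, and anyone who copies the assumption for a similar trial would start from a wrong figure. If 0.2 was really meant, both intervals are wrong, and the 90% power carried over from the protocol is in doubt for a two-sided test.

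**Working it through.** **Inputs.** ICC 0.2, intervals 9–22% and 20–41%, and 44 families: SAP summary of changes. Rates 0.15 and 0.30, 5%, 90%, mean of 4 relatives: protocol section 5.1. Equal allocation: SAP section 1. Assumed: a fixed family size of 4, and both sidedness options.

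**1. From the printed intervals back to the ICC.** For a normal family effect on the logit scale, SD = (logit upper − logit lower)/3.92 and ICC = SD²/(SD² + π²/3).

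- Control: (−1.266 + 2.314)/3.92 = 0.267, so ICC = 0.0715/(0.0715 + 3.290) = 0.021.
- Intervention: (−0.364 + 1.386)/3.92 = 0.261, so ICC = 0.0680/(0.0680 + 3.290) = 0.020.

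Allowing for rounding of the limits, the range is 0.018–0.025. The two arms agree on a value one tenth of the one stated.

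**2. From the ICC forward to the intervals.** SD = √[ICC/(1 − ICC) × π²/3], with the centre μ chosen so that the average over families is 15% or 30%. The limits are the inverse logit of μ ± 1.96 SD.

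- ICC 0.02, SD 0.259: μ = −1.758 gives 9.4–22.3%, and μ = −0.861 gives 20.3–41.3%. Both printed intervals are reproduced after rounding.
- ICC 0.2, SD 0.907: μ = −1.997 gives 2.2–44.5%, and μ = −0.991 gives 5.9–68.7%.
- ICC 0.2 with a beta-distributed family probability (proportion scale): 0.1–58% and 2–76%.
- Reading 0.2 as the logit SD: 11–21% and 23–39%. Reading it as the logit variance: 7–30% and 15–51%.

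No reading of 0.2 that was tried gives the printed intervals. This step does not depend on alpha, sidedness, power or family size.

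**3. Families per arm.** A latent ICC must first be converted to the proportion scale before it enters the design effect 1 + 3 × ICC.

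- Latent 0.02 becomes 0.0085 (control) and 0.0138 (intervention); design effects 1.026 and 1.041.
- Latent 0.2 becomes 0.098 and 0.135; design effects 1.293 and 1.406.
- Proportion-scale 0.2: design effect 1.6 in both arms.

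The unpooled formula is n = (z_α + 1.2816)² × (0.1275 × DE₀ + 0.21 × DE₁)/0.15², divided by 4 for families. The log-odds-ratio formula replaces the bracket by DE₀/0.1275 + DE₁/0.21 and 0.15 by ln(0.30/0.70) − ln(0.15/0.85) = 0.887.

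- Latent 0.02, two-sided, unpooled: 10.508 × 0.3495/0.0225/4 = 40.8. Log odds ratio: 10.508 × 13.00/0.787/4 = 43.4, which rounds up to the plan's 44.
- Latent 0.2, two-sided, unpooled: 10.508 × 0.4601/0.0225/4 = 53.7.
- Latent 0.2, one-sided, unpooled: 8.565 × 0.4601/0.0225/4 = 43.8.

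**4. Power at 44 families (176 relatives) per arm.** Power = Φ(0.15/SE − z_α). For latent 0.2, SE = √(0.4601/176) = 0.0511, so two-sided power is Φ(2.934 − 1.96) = 83% and one-sided power is Φ(2.934 − 1.645) = 90%. For proportion-scale 0.2, SE = √(0.54/176) = 0.0554, so two-sided power is Φ(2.708 − 1.96) = 77%.

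| ICC and scale | Test | Families per arm for 90% | Power at 44 |
|---|---|---|---|
| 0.02 latent | two-sided | 40.8–43.4 | 90–92% |
| 0.2 latent | two-sided | 53.7–56.2 | 82–83% |
| 0.2 proportion | two-sided | 63.0–67.3 | 75–77% |
| 0.2 latent | one-sided | 43.8–45.8 | 89–90% |
| 0.2 proportion | one-sided | 51.4–54.8 | 84–86% |

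Ranges run from the unpooled to the log-odds-ratio formula. Simulated trials analysed by GEE with an exchangeable correlation (1000 per setting, two-sided, family size fixed or varying around 4) gave 82–84% for latent 0.2 with marginal rates of 15% and 30%, and 77–78% for a beta family effect with ICC 0.2.

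**The case against.** The best counter-argument concerns the family count. A reader might infer that 44 families prove that 0.02 was used. They do not. The aim is worded directionally (higher uptake in the experimental group), sidedness is never stated, and a one-sided 5% test at latent ICC 0.2 needs 43.8 families by the unpooled formula. That is as close to 44 as anything obtained at 0.02. At latent 0.02 with a two-sided test, the unpooled formula gives only 41, and it takes the log-odds-ratio formula to reach 44.

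The protocol's earlier figures lean towards a two-sided test. For the 41 and 36 families in section 5.1, two-sided formulas give about 43–45 and 34–36, against 35–36 and 28–30 one-sided. That makes two-sided more plausible, but it does not settle how the revised calculation was done.

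It is also fair to say that the ICC is only a planning input. The GEE estimates the working correlation from the data, so a misprint in the plan changes neither the estimate nor its confidence interval. The Reporting section of the SAP's summary of changes already refers to the manuscript, so the number of families is no longer open.

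All of this stands. None of it reconciles an ICC of 0.2 with the printed intervals, which do not depend on sidedness or family size.

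**Conclusion.** The paragraph contradicts itself. The stated ICC is about ten times the latent-logit value that its own intervals imply (0.020–0.021). The match to 0.02 holds on the latent logit scale only; on the proportion scale the same intervals correspond to roughly 0.009–0.014.

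A reader might go further and conclude that the trial is underpowered. The documents do not support that. If 0.2 is a slip for 0.02, which the intervals suggest, 44 families give 90–92% two-sided power under the planning assumptions. The lower figures of 82–83% (latent) and 75–77% (proportion scale) apply only if 0.2 was the intended value and the test is two-sided, with 15% vs 30% and four relatives per family carried over from the protocol. With a one-sided 5% test at latent 0.2, power is 89–90%, and only the intervals would be wrong.

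**What to change.** Check the sponsor's sample-size calculation and correct the paragraph accordingly.

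- If 0.02 was used, change 0.2 to 0.02 and say that it is on the latent logit scale. The intervals and the 44 families can stay.
- If 0.2 was meant, replace the intervals (about 2–45% and 6–69% for a logit-normal effect, 0–58% and 2–76% for a beta effect) and restate the power at 44 families per arm for the stated scale and sidedness.

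In either case, state the sidedness of the 5% level and the cluster-size assumption. Reporting the observed ICC beside the assumed one would be a useful addition, though it corrects nothing.

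The cost is a corrected sentence or two and possibly a less favourable stated power. No extra families are needed, and the GEE analysis does not change.

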#### Modelling:

In the protocol V1.3, dated 10.08.2022, participation to screening (i.e. primary outcome) was modelled using a logistic mixed effect regression model, using the group as fixed effect and the family as random effect. In the final statistical analysis plan, we proposed to rather use generalized estimating equations (GEE) in order to estimate the marginal probability of participation/detection. This change has been motivated for two reasons. First, interest lies primarily in marginal probabilities (i.e. estimated at the population level) rather than conditional probabilities (i.e. within families) as estimated from mixed effect models. Secondly, unlike mixed effects models, GEE are robust to misspecification of the covariance structure in the data, which makes this approach appealing when the covariance structure is not of particular interest.

#### Reporting

- The per-protocol analysis and the sub-group analyses were not specified in the trial protocol V1.3, dated 10.08.2022. These analyses were therefore newly added in the final statistical analysis plan.

153

154 - These three secondary outcomes mentioned in the trial protocol V1.3, dated 10.08.2022  
155 were not reported in the manuscript:

156 a. the differences in the use of lipid-lowering drug over 6 months

157 b. the change in LDL-cholesterol over 6 months

158 c. the transmission rate of phenotype and genotype into families

159 These outcomes were not directly associated with the intervention aimed to improve  
160 uptake of cascade screening and were therefore not appropriate to include in this  
161 randomized controlled trial report. They will be presented as observational outcomes in  
162 separate publications.

163

164 - Safety endpoint including qualitative research were not collected due to limited  
165 resources. As noted in our manuscript on page 6: “As the potential risks of genetic  
166 cascade screening for FH have already been examined in qualitative studies and are  
167 considered minimal, no specific risks were reported in our trial.”

168

169 - The trial protocol V1.3, dated 10.08.2022 originally included a second randomized  
170 controlled trial to be conducted among index cases with negative genetic test results,  
171 namely those with probable polygenic familial hypercholesterolemia, using cascade lipid  
172 profile testing. However, this additional RCT was not carried out due to insufficient  
173 family participation in the pilot study. This information was reported on page 3 of the  
174 supplementary material

175

176

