#### 3.2 Primary and secondary endpoints

The primary outcome will be the difference in the yield of detection of familial hypercholesterolemia (FH) between arms. The yield of detection is the number of test performed/number of contactable relatives, and will be assessed 6 months after the counselling visit for screening of relatives. Contactable relatives are defined as first-degree family members living in Switzerland.

Secondary endpoints include

- The differences in the number of FH patients identified in each study group. FH patients will be defined according to the Dutch Lipid Network Score of 3 or above (possible, probable or definite FH).
- the differences in the use of lipid-lowering drug over 6 months
- the change in LDL-cholesterol over 6 months
- the transmission rate of phenotype and genotype into families

Safety endpoint include a qualitative assessment of patients' perception and experiences of FH cascade screening.

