- 3) The control arm will also receive information about FH cascade screening as recommended by latest dyslipidemia guidelines.
- 4) Qualitative assessment will be performed in a subgroup of relatives in order to identify psychological risks of unsolicited contact, such as the potential for “right not to know”, anxiety or stigmatization.

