**Table 3a-c: schedule of assessments**

a) **Table 3a:** Schedule of assessments for index cases

| Time (months)                         | >-1            | 0              | +3                   | +9                   |
|---------------------------------------|----------------|----------------|----------------------|----------------------|
| Visit window (weeks)                  | ± 4            | 0              | ± 4                  | ± 4                  |
| Visit (see Figure 2)                  | Screening (V0) | Inclusion (V1) | Index case (V2)      | Follow-up (V2F)      |
| Type of contact                       | Letter         | On site        | On site or telephone | On site or telephone |
| Written patient information           | +              | +              |                      |                      |
| Oral and written patient information  |                | +              |                      |                      |
| Written consent                       |                | +              |                      |                      |
| Inclusion-/exclusion criteria         |                | +              |                      |                      |
| eCRF                                  |                | +              | +                    | +                    |
| Intervention                          |                |                | +                    |                      |
| Self-reported questionnaire baseline  |                | +              |                      |                      |
| Self-reported questionnaire follow-up |                |                |                      | +                    |
| Physical examination                  |                | +              |                      |                      |
| Genetic test                          |                | +              |                      |                      |
| Laboratory documentation              |                | +              |                      | +                    |
| Qualitative research (sample)         |                |                |                      | +                    |

See Appendix 1 for collected variables in each questionnaire/eCRF

b) **Table 3b:** Schedule of assessments for relatives of the monogenic positive FH group

| Time (months)                        | 0                        | +2                       | +8                                                            |

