## **7.2 Risk-benefit assessment**

The risk of the intervention is related to the psychological effects of unsolicited contact by the cascade screening program. This include a breach in the potential “right not to know” leading to anxiety. The stigmatization of genetic information to obtain a life insurance may also be an issue. These risks have been previously studied in qualitative research and can be minimized. Indeed, many relatives are already aware that high cholesterol or coronary artery disease runs in their family. This information will also be taken into account by insurers regardless of the genetic information received via cascade screening.

Regarding unauthorised data access, the recording of relatives' contact details, in addition to their name, could be seen as a breach of confidentiality. To protect relatives' confidentiality, we will not record relatives names and adresses in the cascade screening register until they have positively responded to the index case initiated contact.

The potential benefit of cascade screening for FH have been previously described.

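### The final SAP cites a sentence likely to be read as a no-risk finding, although the safety endpoint was not collected and no assessment of the named psychological risks is shown

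*Combined protocol and SAP*

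**What the plan says.** **Protocol V1.3.** Section 7.2 identifies the hazard: "The risk of the intervention is related to the psychological effects of unsolicited contact by the cascade screening program". It goes on to mention anxiety, the right not to know, and stigmatisation in relation to life insurance. Section 3.2 sets the endpoint: "Safety endpoint include a qualitative assessment of patients' perception and experiences of FH cascade screening". Section 3.4 gives four reasons for regarding the contact procedure as ethically and legally acceptable, and the fourth is this same assessment: "Qualitative assessment will be performed in a subgroup of relatives in order to identify psychological risks of unsolicited contact". Tables 3a to 3c schedule it, in a sample, at the follow-up visit.

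**Final SAP, summary of changes, Reporting.** The endpoint was dropped: "Safety endpoint including qualitative research were not collected due to limited" resources. The next sentence quotes page 6 of the manuscript. It opens by saying that the potential risks of genetic "cascade screening for FH have already been examined in qualitative studies and are" and ends "considered minimal, no specific risks were reported in our trial".

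Sections 1 to 8 of the final SAP contain no safety analysis and no safety conclusion.

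**The concern.** A statement that no risks were reported in a trial is informative only if the trial had a way of finding them. Here the sentence saying that the safety endpoint was not collected is followed directly by a sentence that can pass for a result. The manuscript sentence takes its reason from outside studies but ends on this trial.

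What is at stake is the harms statement. Someone deciding whether to adopt the web platform could take the wording as trial evidence that contact through it is psychologically harmless, including for relatives enrolled as children from age 5. The documents show no data from either arm that could support that conclusion.

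**Working it through.** The plan gives no figure to reproduce and no arithmetic applies, so the check sets the relevant places side by side.

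1. **Which risk does the protocol name?** Psychological effects of being contacted (section 7.2, and the risk/benefit entry of the synopsis).
2. **Which measurement was planned for it?** The qualitative assessment. It is the only safety endpoint in section 3.2. Its stated purpose in section 3.4 is to identify these psychological risks, and the ethical considerations in the synopsis repeat that purpose.
3. **Was it collected?** No (final SAP, summary of changes, Reporting). The reason given is resources.
4. **Could another route have captured the same risk?**
   - *SAE reporting (section 6.2).* The criteria are death or threat to life, new or prolonged hospitalisation, lasting disability, and congenital anomaly. Anxiety, distress over unwanted knowledge, or stigmatisation would qualify only if one of these followed.
   - *Non-serious adverse events.* Section 6.2 defines and grades them, but its documentation and reporting duty is written for SAEs. Tables 3a to 3c have no adverse event row, so systematic collection of non-serious events is not shown.
   - *Follow-up questionnaires.* These are scheduled in Tables 3a to 3c. Appendix 1 only refers to the forms, so their content on anxiety or related matters cannot be judged.
5. **Does the final SAP or its summary of changes cite results from any of these routes?** No.
6. **Can the outside studies stand in for the endpoint?** Sections 3.4 and 7.2 already cite qualitative research on these risks, and the protocol nevertheless planned its own assessment. Those studies can support a statement about the literature. They cannot support a statement about what happened in this trial.

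The quoted sentence therefore has two readings. If it means that the authors did not report on risks, it is true but badly put. If it means that no risks came to light, the documents show no collected assessment of the psychological risks on which it could rest.

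**The case against.** The strongest defence is grammatical. The full sentence begins with a causal clause: because others have studied the risks, none were reported here. Earlier research can explain why authors left risks out; it cannot cause a trial to observe none. Read strictly, the sentence justifies an omission. This stands as far as it goes, and is why the fault is ambiguity rather than a plain false claim. It does not remove the need to rewrite, because the wording invites the other reading on a question of harm.

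Two further points stand. The non-collection is openly disclosed in the sentence before, within a list of departures from protocol V1.3, so a reader who inferred concealment would be wrong. And the sentence belongs to a manuscript that is not among the documents, so any limitation stated there cannot be seen.

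A reader might also infer more than the documents support:

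- *That nothing in the trial looked for harm, so it has no evidence on harms of any kind.* SAE reporting and an annual safety report were required (sections 6.2 and 6.3), and the questionnaires have not been seen. The gap shown concerns the psychological risks of contact.
- *That a zero-event upper confidence limit can size the gap.* It cannot. The endpoint was qualitative, was planned in a sample of unstated size, and concerned a risk borne by everyone contacted, including those who declined testing. A bound computed on tested relatives would use the wrong denominator and ignore clustering by family.
- *That the summary of changes conflicts with the protocol merely by dropping the endpoint.* A declared change is not an error. The problem lies within the current text: non-collection next to a sentence that reads as a finding.

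**Conclusion.** The point holds as a matter of reporting. The planned safety endpoint was not collected, and the sentence offered in its place is likely to be read as a trial finding of no risk. The documents contain nothing that would support such a finding for the psychological risks the protocol names. There is no evidence here that the platform caused harm; the trial is uninformative on that question as far as the documents show.

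The conclusion rests on two assumptions: that the unseen questionnaires did not measure these risks, and that no safety results exist beyond what the SAP mentions. If either is wrong, those data should be shown and the statement limited to what they cover. A statement confined to SAEs could be supported if that reporting was run and its results are given.

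The primary analysis of screening uptake and the secondary analysis of new cases identified do not change. What changes is what the trial can say about harm.

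**What to change.** 1. Replace the sentence, in the manuscript and where the SAP cites it, with: *The psychological risks of contact were not assessed in this trial, so it provides no evidence on them; earlier qualitative studies considered them minimal.*
2. Report by arm the SAEs documented under section 6.2, including zero counts, or state that this route was not run. Do not present non-serious adverse events as systematically collected.
3. Name the uncollected safety endpoint as a limitation in the trial report. The summary of changes already discloses the non-collection, so nothing further is needed there.

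The cost is a few sentences and at most one small table drawn from reporting the protocol already required. No analysis is rerun. The price to the authors is a less favourable safety statement.
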